**Figure 1 F1:**
[figure not shown]
**Study flow chart.** PROMS, patient-reported outcome measures.

PARot study assessments will include patient-reported outcome measures (PROMs), histological examinations, functional assessments and patient satisfaction and health economic questions. Evaluation of routine basic blood tests will also be included in the PARot assessments. A full blood count (taken as part of routine preoperative assessment and not a study intervention) will indicate the presence of clotting substances and any PRP contraindications the patient may have.

Patients will be required to attend a clinic appointment for assessments at 6 weeks and at 3 and 6 months post treatment. A postal questionnaire (containing the Oxford shoulder score, Oxford satisfaction index and EQ 5D) will also be sent out at 12 months post treatment. Clinical assessments and any adverse reactions or side effects can be documented. Table 1 outlines the outcome measures and their correlating time points.

**Table 1 T1:** Outcome assessments

	**Baseline**	**6 weeks**	**3 months**	**6 months**	**12 months**
**Oxford shoulder score**	X	X	X	X	X
**Tissue biopsy**	X^a^		X^b^		
**Pain diary**		X			
**Clinical examination**	X	X	X	X	
**Oxford satisfaction index**	X	X	X	X	X
**EQ 5D**	X	X	X	X	X
**Complications**	X	X	X	X	X
**Venous blood sampling**	X				
**Ultrasound**	X		X	X	

^a^ Ultrasound-guided biopsy during surgery.

^b^ Ultrasound-guided biopsy at follow-up visit.

The primary outcome measures are the Oxford shoulder score (OSS) assessed at 12 months and the histological assessments of the biopsy tissue. The Oxford shoulder score is a condition-specific questionnaire providing a total score based on the patient’s subjective assessment of pain and activities of daily living (ADL) impairment. The range of available scores is 0 (worst) to 48 (best) [11]. The score is reliable and valid. The questionnaire will be administered to patients at the baseline and during their follow-up visits.

Secondary outcomes involve basic histological tests to assess vascularity, antibodies and neural tissue and cell creation [12]. Tissue samples will be taken at the baseline (during surgery) and again 3 months later. Secondary outcomes also include radiological and clinical assessment of impingement syndrome to assess the progression of any cuff tear. Data related to patient satisfaction and resource use involved in each treatment arm will also be collected at the baseline and again at follow-up visits.

The PARot study will include patients diagnosed with subacromial impingement syndrome or a partial-thickness tear who have failed conservative treatment. The inclusion criteria are the following:

• Patients with shoulder impingement syndrome or a partial-thickness rotator cuff tear.

• Diagnosis confirmed using ultrasound scan by a trained member of the research team.

• Failed conservative treatment.

• Listed for arthroscopic subacromial decompression surgery.

• Male or female, aged 35 to 75 years old.

Patients may not enter the study if any of the following apply:

• Full thickness rotator cuff tears.

• Participants with a history of significant trauma. (fracture, dislocation, instability and so on), surgery, osteoarthritis or other significant pathology of the affected shoulder not related to the rotator cuff.

• Patient is unable to consent.

• No conservative treatment.

• Previous surgery on affected surgery.

• Contraindications to PRP (listed below).

PRP contraindications:

• History of diabetes mellitus.

• Platelet abnormality or platelet count <100 × 10^9^/l.

• Hematological disorder.

• Serum hemoglobin <11 g/dl.

• Use of systemic cortisone.

• Use of any anticoagulant.

• Evidence of gangrene, ulcers or peripheral vascular disease.

• History of hepatic or renal impairment or dialysis.

• Patient is known to have a psychological, developmental, physical, emotional or social disorder that may interfere with compliance with study requirements.

• History of alcohol or drug abuse.

• Patient has a religious or cultural conflict with the use of platelet gel or blood products.

• Patient has inadequate venous access for blood draw.

• Patient is currently receiving or has received radiation or chemotherapy within the last 3 months prior to the study.

• Female participants who are pregnant, lactating or planning pregnancy during the course of the study.

• Any other significant disease or disorder that, in the opinion of the investigator, may either put the participant at risk because of participation in the study, or may influence the result of the study, or the participant’s ability to participate in the study.

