### The Oxford shoulder score

The OSS at 12 months is the primary outcome measure and the primary hypothesis is based upon this evaluation. The design is a simple two-group cross-sectional comparison. The data will be first checked for normality using histograms and Shapiro–Wilk tests. Independent *t*-tests (assuming normal distribution and equal variance) will then be performed to test the hypothesis that there is no difference in the mean OSS between the two groups. The null hypothesis will be rejected for significance set at α = 0.05.

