### Histology assessments

The tendon structure will be examined with basic histology by staining specimens with hematoxylin and eosin, toluidine blue and Congo red. Immunohistochemical analysis will also be performed using specific antibody markers such as vascular endothelial markers (CD 34), macrophage-associated markers (CD 68) [12] as well as neural tissue (S100) and cell proliferation (PCNA). Statistical analysis with *t*-tests will be used with significance set at α = 0.05.

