### Secondary outcome measures

Descriptive statistics will be presented for the secondary endpoints but no formal significance tests will be performed. The sample size is insufficient to test hypotheses for this categorical data but some valuable indication of effect may be observed.

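### Histology is called both a primary and a secondary outcome, and its planned tests at 0.05 fit neither label cleanly; its status must be settled before analysis

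*Protocol article*

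**What the plan says.** Five places in the protocol article bear on the status of histology.

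- Methods/design, after Table 1: "The primary outcome measures are the Oxford shoulder score (OSS) assessed at 12 months and the histological assessments of the biopsy tissue".
- Methods/design, the following paragraph: "Secondary outcomes involve basic histological tests to assess vascularity, antibodies and neural tissue and cell creation".
- The Oxford shoulder score: "The OSS at 12 months is the primary outcome measure and the primary hypothesis is based upon this evaluation". The test there is an independent t-test, and "The null hypothesis will be rejected for significance set at α = 0.05".
- Histology assessments: tendon structure is examined by "staining specimens with hematoxylin and eosin, toluidine blue and Congo red", and immunohistochemistry uses an open list of antibody markers, of which four are named (CD 34, CD 68, S100, PCNA). For these data t-tests "will be used with significance set at α = 0.05", the same level as for OSS.
- Secondary outcome measures: "Descriptive statistics will be presented for the secondary endpoints but no formal significance tests will be performed". The reason given is that the sample is too small for hypothesis tests on what the section calls categorical data.

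Statistics and analysis sizes the trial on OSS only. Analysis of endpoints leaves the full analysis to an SAP, to be approved before any analysis.

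**The concern.** A superiority trial needs one unambiguous statement of which result decides success. Here the plural primary outcomes in Methods/design and the single primary outcome in the OSS section cannot both be right. The secondary list also covers much of what the histology section measures: vascularity (CD 34), neural tissue (S100) and cell proliferation (PCNA).

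The stake is how the trial is reported. Suppose the OSS comparison is null and one marker reaches p < 0.05. A report that follows Methods/design could present this as a positive primary outcome; one that follows the OSS section could not. Nothing in the article rules out the former.

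**Working it through.** **1. The plan's own figure.** Inputs from Statistics and analysis: difference 3 points, SD 3 points, α = 0.05, power 0.80. Sidedness is not stated; two-sided is assumed because a one-sided test gives 13 per arm and does not fit.

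- Normal approximation: n = 2 × (1.960 + 0.842)² × (3/3)² = 15.7, so 16 per arm.
- Exact two-sample t-test: n = 16.7, so 17 per arm, with power 0.807.

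The stated 17 per arm reproduces. It is a calculation for OSS alone at the full 0.05.

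**2. If histology is primary.** The article gives no rule for combining the outcomes.

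- *Either suffices.* With k independent tests at 0.05, the chance of at least one false positive is 1 − 0.95^k.
  - k = 2 (OSS and one histology test): 1 − 0.95² = 0.0975, or 9.8%.
  - k = 5 (OSS and the four named markers): 1 − 0.95⁵ = 0.226, or 22.6%.
- *Both must succeed.* The chance of a false claim stays at or below 5%, so there is no inflation.

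Markers from the same biopsies are unlikely to be independent. A simulation of equally correlated t-tests with 17 per arm (40,000 runs) gave:

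| Assumed correlation | 2 tests | 5 tests |
|---|---|---|
| 0 | 9.8% | 22.6% |
| 0.3 | 9.5% | 21.2% |
| 0.5 | 9.1% | 18.7% |
| 0.8 | 7.7% | 12.9% |

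The correlations are assumptions. So is the number of tests: the article does not say how many numerical readouts will be tested.

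**3. If histology is secondary.** The primary claim then rests on one OSS test at 0.05, with no inflation. But the histology section plans t-tests at 0.05, while the section on secondary measures says its endpoints get none. The two agree only if the no-testing statement covers categorical endpoints alone. Its stated reason hints at that; its opening sentence, which makes no exception, does not.

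**4. The readings are alternatives.** The inflation in step 2 and the conflict in step 3 do not hold together. One reading or the other must be chosen, and on each the article needs correcting or completing.

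**The case against.** The best defence is that the OSS section settles the matter. It ties the primary hypothesis to 12-month OSS, and the sample size agrees. On that view the reference to histology as primary is loose wording and the type I error of the primary test is 5%. This stands as evidence of what was probably intended, and it supports the fix. It does not remove the plural statement in Methods/design.

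A second defence is that a lead marker, a testing order or an adjustment belongs in the SAP. That is fair, and their absence from the article is not criticised here. The outcome labels and the 0.05 level for histology, however, are already stated, and any SAP would have to depart from one of the statements.

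Stronger readings are tempting but not supported:

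- *That the primary type I error is inflated as a matter of fact.* No either-suffices rule is stated, so inflation is a conditional risk.
- *That familywise error is 33.7%.* This is 1 − 0.95⁸ for OSS, four markers and three stains. It assumes independence and a separate t-test for each stain, but the stains are described only as a means of examining tendon structure.
- *That OSS power is below 80%.* Splitting α to 0.025 would give 0.71 at 17 per arm and 0.79 at 20, but nobody plans such a split.
- *That the histology tests plainly breach the no-testing rule.* They do so only if histology is secondary and the reference to categorical data is not read as limiting the rule.

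**Conclusion.** The contradiction over the status of histology is explicit and should be resolved before analysis. Its size depends on the reading. If histology is primary and either outcome is enough, familywise error is 9.8% for two independent tests. For OSS plus the four named markers it is about 23% if independent, or roughly 13% to 21% at assumed correlations of 0.8 to 0.3. If histology is secondary, the primary error rate is intact and the fault is an inconsistency between two analysis sections, softened by the reference to categorical data. The sample size is not in error.

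**What to change.** Before any analysis, through a dated amendment or in the SAP:

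1. State 12-month OSS as the sole primary outcome, tested at 0.05, wherever outcomes are ranked: both outcome paragraphs of Methods/design and the OSS section.
2. Label histology as secondary or mechanistic throughout.
3. Report the markers as between-group estimates with 95% confidence intervals and no significance claim. If tests are kept, adjust across all tested markers, for example by Holm; with four markers the smallest p-value is then compared with 0.05/4 = 0.0125.
4. Reword Histology assessments and Secondary outcome measures to agree: either no tests on histology, or a named exception for the adjusted ones. Say whether the no-testing rule is limited to categorical endpoints.

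Sample size, biopsies and visits are unchanged; 17 evaluable per arm (20 recruited) still gives power 0.81 for OSS. The downside is that a nominally significant marker can no longer be claimed as a primary success.

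Timing needs care. Trial status reports completed follow-up on 40 patients, the whole target, and assessors are not blinded. The change should therefore carry its date and reason and record that it was made before outcome data by arm were examined; otherwise removing a published primary outcome could itself look data-driven.

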## Discussion

### Definition of end of study

The end of the trial is the date of the last visit or telephone follow-up of the last participant.

### Discontinuation or withdrawal of participants from study treatment

Each patient has the right to withdraw from the study at any time. In addition, the investigator may discontinue a patient from the main analysis at any time if the investigator considers it necessary for any reason including:

• Development of any PRP contraindications.

• Significant protocol deviation.

• Significant non-compliance with treatment regimen or study requirements.

• An adverse event that results in an inability to continue to comply with study procedures.

• Disease progression that requires discontinuation of the study medication or results in inability to continue to comply with study procedures.

• Lost to follow-up.

No procedures or observation will continue to be required following withdrawal from the trial. Data collected before withdrawal from the trial will be used in the statistical intention-to-treat analyses and analysis of all participants receiving the study treatment.

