## Methods/design

PARot is a parallel blinded superiority-type randomized controlled trial. The two groups are: arthroscopic subacromial decompression surgery and arthroscopic subacromial decompression surgery with application of PRP.

The study will run for 3 years. Recruitment will be for 24 months with final follow-up at 1 year post surgery. The final year will involve collation and analysis of the data. Only patients will be blinded as to whether they received PRP or not.

Patients identified for the study will have failed conservative treatment for their shoulder impingement or partial-thickness tear and will be listed for subacromial decompression surgery. Conservative treatment may include physiotherapy and injections of steroid and or local anesthetic. The routine step following failed conservative treatment would usually involve being put on the waiting list for surgery (SAD).

Patients will be identified in, and recruited from, the shoulder outpatient clinics at the Nuffield Orthopaedic Centre, Oxford University Hospitals (OUH) NHS Trust, Oxford. Diagnosis of shoulder impingement or partial-thickness tear will be confirmed with ultrasound in the clinic and the patient will be put on the waiting list for surgery. A surgical member of the research team will introduce the trial to the patient and refer them to a research nurse for recruitment.

Informed consent procedures, baseline assessments (including the Oxford shoulder score) and randomization are performed up to 3 days prior to surgery due to organizational requirements in relation to operating schedules and required equipment. Randomization is undertaken using sealed envelopes based on a simple computer-generated randomization list.

Routine perioperative care will proceed and the patient will have their operation as planned.

As randomization occurs very close to the point of treatment, patients will be followed up in clinic at 6 weeks and at 3 and 6 months post treatment. Patients will be blinded to the treatment they are allocated to. Assessors and surgeons are unable to be blinded in this instance. All patients will remain on the waiting list for surgery as per standard care and may have their surgery at the planned date. A summary of the study design is portrayed in the flow chart (Figure 1).

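### Investigators who know the allocation may remove randomised patients from the main analysis for any reason, which contradicts the promised intention-to-treat analysis

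*Protocol article*

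**What the plan says.** The section on discontinuation or withdrawal from study treatment states that "the investigator may discontinue a patient from the main analysis at any time if the investigator considers it necessary for any reason including" six listed reasons. Four bear directly on this point:

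- a ground tied to worsening of the condition: "Disease progression that requires discontinuation of the study medication or results in inability to continue to comply with study procedures"
- a ground tied to conduct of the trial: "Significant protocol deviation"
- a ground tied to safety: "An adverse event that results in an inability to continue to comply with study procedures"
- a ground tied to suitability for PRP: "Development of any PRP contraindications"

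The other two are significant non-compliance and loss to follow-up. The section then says that nothing further need be observed after withdrawal, and closes: "Data collected before withdrawal from the trial will be used in the statistical intention-to-treat analyses", together with an analysis of everyone who received the study treatment.

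On blinding, Methods/design says that only patients are blinded and adds: "Assessors and surgeons are unable to be blinded in this instance". The section on the Oxford shoulder score makes the 12-month OSS the primary outcome, compared between two groups by an independent t-test. Among the secondary outcomes, Methods/design includes: "Secondary outcomes also include radiological and clinical assessment of impingement syndrome to assess the progression of any cuff tear".

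**The concern.** The power has no time limit and no closed list of reasons, and the decision need not be made blind to allocation. It acts on membership of the main analysis, not only on treatment or visits. Several listed events arise after randomisation and may be related to outcome. Cuff-tear progression, for example, is itself a secondary outcome.

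The OSS is completed by blinded patients, but that does not help if unblinded staff decide whose OSS is analysed. Table 1 also schedules the OSS at 6 weeks, 3 months and 6 months, so a patient's course may be known well before the primary time point. Selection of this kind breaks the randomised comparison and can create or hide a difference. In a trial of about 20 per arm, a few removals can matter if they are related to outcome.

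**Working it through.** **1. The statements side by side.** One sentence allows discretionary removal from the main analysis. The closing sentence of the same section keeps withdrawn patients' data in intention-to-treat analyses. A patient cannot be both removed at discretion and retained as randomised.

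**2. Whether the closing sentence repairs the rule.** It keeps only data collected before withdrawal, and no observation is required afterwards. The primary test uses one time point, 12 months. A patient removed earlier therefore has no primary value and drops out of the t-test.

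**3. Whether the rule is really about stopping treatment.** PRP is applied once, during surgery. After that, little study treatment remains to be stopped, so the rule acts mainly on follow-up and analysis.

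**4. The plan's own sample size** (Statistics and analysis: difference 3, SD 3, alpha 0.05, power 0.8; two-sided testing is assumed because sidedness is not stated).

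- Normal approximation: n = 2(1.96 + 0.84)² × 3²/3² ≈ 15.7, so 16 per arm.
- t-test: 16.7, so 17 per arm, with power 0.807. This reproduces the stated 17.
- Allowance for losses: 17/0.85 = 20 per arm, or 3 of 20 (15%). If all 20 per arm are analysed, power is about 0.87.

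**5. Illustration of selective removal.** Assumptions: normal scores, SD 3, 20 per arm, no true effect, removals from the PRP arm only, pooled t-test at two-sided 0.05, 100,000 simulated trials. The number and pattern of removals are assumed.

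| Removed from the PRP arm | Shift (points) | Two-sided rejection | Rejection favouring PRP |
|---|---|---|---|
| None | 0.00 | 5.0% | 2.4% |
| 1 at random from worse half | +0.13 | 5.1% | 3.2% |
| 2 at random from worse half | +0.26 | 5.4% | 4.2% |
| 3 at random from worse half | +0.41 | 6.5% | 5.7% |
| Worst 1 | +0.29 | 6.8% | 5.4% |
| Worst 2 | +0.55 | 10.1% | 9.3% |
| Worst 3 | +0.78 | 14.3% | 13.9% |

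A second run of the worst-case rows gave 6.8%, 10.0% and 14.5%.

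To read the shifts: removing k patients who lie on average m points below their arm's mean raises that mean by k × m/(20 − k). For k = 3, a shift of 0.41 means m = 0.41 × 17/3 ≈ 2.3 points, and a shift of 0.78 means m ≈ 4.4 points. Against the 3-point target, the shifts are 0.41/3 ≈ 14% and 0.78/3 = 26%. Removal unrelated to outcome would cost power but would not bias the difference.

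**The case against.** The strongest reply is that the words about the main analysis are a drafting slip. The section heading refers to study treatment, most of the bullets are ordinary reasons for ending participation, and the section ends on intention-to-treat. The section on analysis of endpoints also leaves full detail to an analysis plan approved before any analysis, which is not shown and may define the populations properly. This lowers certainty about what will be done. It does not cure the text: an analysis plan would either inherit the rule or contradict the protocol.

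Four stronger readings are tempting, and the documents do not support them:

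- A reader might infer that any adverse event or any progression is a listed ground. Both are listed with conditions: an adverse event must prevent compliance, and progression must either require stopping study medication or prevent compliance. The list is open-ended all the same.
- A reader might infer that the PRP-contraindication ground applies to one arm only. These contraindications are exclusion criteria for all patients and can arise in either arm. What remains is that staff who know the allocation may act on them differently.
- A reader might count loss to follow-up as part of the selection problem. Such a patient lacks a 12-month score whatever the investigator decides, so this is ordinary missing data.
- A reader might take 10% to 14.5% as the expected error rate. Those figures require the lowest 12-month scores to be identified and removed from one arm alone. The 12-month OSS is a postal questionnaire completed by a blinded patient, and before it arrives an investigator has only earlier, imperfect information. The allowance of three per arm is also stated for losses to follow-up, not for discretionary removals.

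**Conclusion.** The point holds on the text. A stated rule lets unblinded staff decide who enters the main analysis, no other section limits it, and it conflicts with the intention-to-treat sentence in the same section. That the investigator is unblinded follows from the statement that only patients are blinded, since the explicit list names assessors and surgeons.

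Confidence is high on the contradiction and low on the size of any bias. If three outcome-related removals fell in the PRP arm, a plausible illustration is about +0.4 points and 6.5% false positives, with about +0.8 points and 14% to 14.5% as an upper bound. Both rest on the plan's SD of 3, on one-sided removal and on an assumed count. Nothing shows that any patient has been or will be removed in this way, and the documents do not support inferring a planned outcome-driven exclusion. The correction is needed because the rule governs the primary comparison, whatever the simulated rates.

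**What to change.** - **Delete the power** to remove a patient from the main analysis. State that the listed reasons may end study procedures but do not change the analysis set.
- **Define the primary analysis** as all randomised patients with a 12-month OSS, in their allocated arm, with missing scores handled by a rule fixed before analysis.
- **Keep collecting the outcome.** Send the already planned 12-month postal OSS to removed patients unless they withdraw consent to follow-up. The Trial status section reports follow-up completed on 40 patients, the full target, so for many this may be too late. In that case, fix the analysis set before any analysis is run.
- **Confine deviation-based exclusions** to a labelled per-protocol sensitivity analysis, decided without sight of outcome by allocation.
- **Reconcile with the section on subacromial decompression surgery.** It excludes full-thickness tears found at operation, yet Methods/design places randomisation up to 3 days before surgery. Report these post-randomisation exclusions by arm and state how they enter the analysis set.

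The cost is protocol and analysis-plan wording and, where still possible, a few questionnaires. The small downside is that patients with deviations stay in and may slightly dilute the effect. The sample size does not change.
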